### Relevant concomitant care permitted or prohibited during the trial {11d}

Implementation of the WalkingPad program will not require a change in usual care pathways (including the use of any medication) in the three arms of the study. Thus, there will be no restrictions regarding concomitant care during the trial.

### Provisions for post-trial care {30}

There is no anticipated harm and compensation for participating in the trial. However, post-trial care encompasses the following responsibilities: referring patients for appropriate follow-up care (other medical specialty or counseling) or providing alternative therapeutic measures (change of medication or consideration of surgery).

### Outcomes {12}

#### Primary outcome

The primary endpoint will be the WalkingPad-induced change in PFWD, FWD, and MWD measured using a standardized treadmill test and the 6-min walk test (6MWT). PFWD is defined as the distance walked at the onset of claudication pain. FWD is defined as the distance at which a patient chooses to stop because of the discomfort caused by claudicating pain. MWD is defined as the distance at which claudication pain becomes so intense that the patient is forced to stop.

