PFWD	*6-min walk test (6MWT)*	The 6MWT is a performance-based measure that evaluates the functional capacity of the individual to walk over a total of 6 min on a 100 ft (≈30 m) hallway, providing information regarding all the systems during physical activity [35]. The participants will be instructed to walk back and forth along the hallway to achieve the greatest distance possible. The participants will be allowed to stop and rest while the stopwatch continues to run. The American Thoracic Society guidelines will be used [38]. No encouragement through standardized verb phrases will be given because the aim is for the test to be as similar as possible to what happens in a real environment.
**Secondary outcomes**	**Measure**	**Brief description**
Physical and Mental Quality of Life	*Short-Form Health Survey (SF-36)*	This instrument consists of 36 items with different response scales assessing eight health concepts: limitations in physical activities because of health problems,limitations in social activities because of physical or emotional problems, limitations in usual role activities because of physical health problems, bodily pain, general mental health (psychological distress and well-being), limitations in usual role activities because of emotional problems, vitality (energy and fatigue), and general health perceptions. The SF-36 has been widely used in studies with this population and has excellent psychometrics [39, 40].
Vascular Disease-specific Quality of Life	*Vascular Disease-Specific Quality of Life Questionnaire (VAscuQoL-6)*	This is a specific measure of health-related QoL for patients with PAD, consisting of six items with different response scales [41, 42]. The total score ranges from 6 to 24, with higher results corresponding to a higer quality of life associated with arterial disease. The Brazilian-Portuguese version of the VascuQoL-6 presents adequate valid and reliable indicators allowing its use in patients with PAD with intermittent claudication symptoms [43].

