**Fig. 2 Fig2:**
[figure not shown]
Flow diagram of the clinical trial

The primary outcomes will be measured by two tests. The walking distance measured with a standardized treadmill test [34, 35] is a widely used tool for functional assessment and monitoring of exercise rehabilitation, where PFWD, FWD, and MWD are objective measures of improvement. In turn, the 6MWT is an individualized test that assesses the submaximal level of functional capacity [35, 38]. The patient chooses the intensity of the exercise and can rest during the test, which better reflects the functional level of exercise practiced in daily physical activities. Therefore, we chose to use both measures (walking distance measured with the treadmill test and walking distance measured with the 6MWT) not only because they complement each other but also because both provide different and valuable information.

The primary outcomes will reflect the effectiveness (beneficial effect) and not the harm (adverse effect) of the intervention. The change achieved in primary outcomes from baseline to 3 and 6 months will be a valid, reproducible, and relevant result for the target population and healthcare professionals. The amount of change achieved will be represented in a continuous variable that will facilitate comparisons and grouping of results across studies, trials, and meta-analyses. Data collection forms can be requested from the responsible investigator.

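### The 6-minute walk test primary endpoint is described in three incompatible ways, and the pain-defined distances attached to it need not occur on that test

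*Protocol article*

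**What the plan says.** The Primary outcome section defines the endpoint as the "change in PFWD, FWD, and MWD measured using a standardized treadmill test and the 6-min walk test (6MWT"). It does not divide the three distances between the two tests. Each distance is then tied to a pain event:

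- For PFWD, the event is that claudication pain begins.
- For FWD, it is a halt that the patient elects to make on account of that pain.
- For the third, the wording is: "MWD is defined as the distance at which claudication pain becomes so intense that the patient is forced to stop".

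Table 1 does divide them. Its treadmill row carries MWD, PFWD and FWD. Its 6MWT row carries PFWD alone. That row says the test "evaluates the functional capacity of the individual to walk over a total of 6 min on a 100 ft" corridor. On rests it says: "The participants will be allowed to stop and rest while the stopwatch continues to run".

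The data collection text after Fig. 2 calls both tests primary. It presents PFWD, FWD and MWD as what the treadmill measures, and refers to the 6MWT result only as a walking distance. It describes the 6MWT as submaximal: "The patient chooses the intensity of the exercise and can rest during the test".

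**The concern.** Two problems meet here. The first is that a reader cannot tell which 6MWT variable is primary: three distances, one distance, or a walking distance that is not further specified.

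The second is that an endpoint defined by a pain event has a value only if the event happens. A treadmill test in which patients walk to near-maximal pain is built to produce those events. A corridor test that ends on the clock, at a pace the patient picks, is not. Patients who get through 6 minutes without the event would have no value, and they are likely to be those who walk best or have improved most. Leaving them out would remove good responders selectively. Entering their 6-minute distance as though it were the pain-defined distance would put a ceiling on them. Either could distort the comparison between arms, in a trial whose stated minimal clinically important difference is only 20 m.

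**Working it through.** The protocol gives no figure on this point to reproduce, so the check is mainly a comparison of sections.

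**Step 1: which variable is primary on the 6MWT?**

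| Place | Treadmill | 6MWT |
|---|---|---|
| Primary outcome section | PFWD, FWD, MWD | PFWD, FWD, MWD |
| Table 1 | MWD, PFWD, FWD | PFWD |
| Text after Fig. 2 | PFWD, FWD, MWD | a walking distance, not specified |

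The treadmill column agrees throughout and the 6MWT column differs in every row. The Objectives and Statistical methods sections name MWD, PFWD and FWD without naming a test, so they do not settle it.

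**Step 2: does the test yield the defined quantity?** Each definition is set against a test that stops at 6 minutes and permits rests.

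- MWD needs a forced stop. A patient never forced to stop has no MWD.
- FWD needs a chosen stop for claudication discomfort. A patient who stops voluntarily for that reason does have an FWD. One who never does so has none.
- PFWD needs only the onset of pain. It can be observed on a timed walk, and is undefined only for a patient without pain within 6 minutes.
- A patient who rests and resumes has both a first-stop distance and a longer total distance. The first-stop distance could be recorded, but the article does not say which of the two counts.
- Total distance in 6 minutes exists for every patient who starts the test. No section clearly names it as the endpoint.

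**Step 3: is finishing without a forced stop plausible?** Inputs are the Table 1 treadmill steps (1.0, 1.6 and 2.4 km/h for 2 minutes each, then 3.2 km/h), the entry range for treadmill MWD (50 to 500 m) and the upper randomization stratum (276 to 500 m).

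- Distance in the first 6 minutes = sum of speed × 1000/60 × 2 = 33.3 + 53.3 + 80.0 = 166.7 m.
- Rate after that = 3.2 × 1000/60 = 53.3 m/min.
- Time to reach 276 m = 6 + (276 − 166.7)/53.3 = 8.05 min.
- Time to reach 500 m = 6 + (500 − 166.7)/53.3 = 12.25 min.

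Patients with a treadmill MWD above about 167 m, including the whole upper stratum, therefore walk for more than 6 minutes on that test before a forced stop.

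Corridor pace is self-chosen and not stated. Over an assumed 2.4 to 4.8 km/h, 6 minutes of unbroken walking covers 2.4 × 100 = 240 m to 4.8 × 100 = 480 m, which lies inside the entry range. Some eligible patients could plausibly finish without a forced stop. The share cannot be calculated from the document.

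**The case against.** The strongest reply is that Table 1 already settles the matter. It assigns outcomes test by test and gives the 6MWT only PFWD, so the sentence in the Primary outcome section may be a loose summary. PFWD does not need a stop and can be observed on a timed walk. Scoring rules for patients without an event are commonly left to a full protocol, test manual or SAP, and their absence from an article is no defect.

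Much of this stands. A reader might infer that FWD and MWD are firmly fixed as 6MWT primary endpoints. The documents do not support that, because Table 1 and the text after Fig. 2 point the other way. Nor does permission to rest by itself make a value undefined. The missing scoring rule is not held against the article either.

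What the reply does not remove is the contradiction, which is in the article's own text and concerns a primary endpoint. The two readings that name the distances also leave a gap. The Primary outcome section asks the test for quantities it does not reliably yield, and Table 1's PFWD is undefined for patients who finish without pain. The third reading, an unspecified walking distance, is not a defined endpoint until someone says which distance it is.

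**Conclusion.** The point holds as an inconsistency in a primary endpoint, together with definitions that fit a fixed-time test poorly. The treadmill endpoints are unaffected. It should be corrected before analysis, but it does not undermine the trial as a whole.

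The direction of any harm can be argued: patients without a value are likely to be the better performers, so exclusion or capping could bias or shrink arm differences. The size cannot be stated. A reader might go further and compute a dilution by entering finishers at their 6-minute distance as if it were MWD. That would need a scoring rule that no section gives and a walking pace that no section reports. It would also treat treadmill MWD, reached at stepped speed and then rising grade, as interchangeable with flat self-paced walking. No such figure is claimed here.

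**What to change.** 1. Reword the Primary outcome section so that it agrees with Table 1 and the text after Fig. 2: FWD and MWD come from the treadmill test only, as Table 1 already has it.
2. Name the 6MWT outcome in all three places as total distance walked in 6 minutes, rests included.
3. If PFWD on the 6MWT is kept, state that a patient who finishes without pain is right-censored at the distance walked in 6 minutes and is not treated as missing. That variable then needs an analysis that accommodates censoring, which the planned mixed ANOVA does not.

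The cost is a change of wording in the outcome section, Table 1 and the text after Fig. 2. Total distance comes from the test as already described, so no extra assessment is needed. The downside is two fewer nominal 6MWT endpoints, FWD and MWD. The treadmill's own 500 m limit on pain-free walking is a separate matter that this change does not address.

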**Methods:**

This is a single-center, prospective, three-arm, single-blind, randomized, controlled, superior clinical trial with stratified and blocked random allocation. Three hundred participants with PAD and IC will be recruited from an Angiology and Vascular Surgery Department, Centro Hospitalar Universitário Porto (CHUPorto), Porto, Portugal. All patients will receive the same medical care recommended by  current guidelines. Participants in all three groups will receive a personalized prescription for an HBET program and a behavioral change and motivational intervention. Participants in experimental groups 1 and 2 will receive a smartphone with the WalkingPad app to monitor exercise sessions. Experimental group 2 WalkingPad app will have a built-in virtual assistant that will promote behavioral change and provide motivational support. Participants allocated to the active control group will not receive the m-health tool, but a practice diary to encourage monitoring. The  program will last for 6 months with three evaluation moments (baseline, 3, and 6 months). The primary outcome will be the change in distances walked (maximal and pain-free) from baseline to 3 and 6 months. Secondary outcomes will be changes in quality of life, patients’ perception of resistance, and walking speed.

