## Statistical methods

### Statistical methods for primary and secondary outcomes {20a}

The first step in the data analysis plan will be the screening of data to detect errors and missing values, although missing data is not expected in the questionnaires, as the data collection will be carried out in person with a researcher who will guarantee its complete completion. Missing values may be present when a participant withdraw or refuse to participate in the assessment, or missing values in physical tests due to physical limitations or difficulties in performing physical performance tests (e.g., treadmill test). Second, a summary of baseline sociodemographic, clinical, physical, and psychological variables will be provided through descriptive statistics. Third, comparisons will be made between the three groups to examine whether there are differences between the groups at baseline in all variables. As the sample was stratified, differences in fundamental variables such as age and maximal walking distance are not expected to be found. In addition, differences at baseline between participants who will complete the study and those who drop out will be examined. Fourth, primary outcome analyses will be conducted on an intention-to-treat basis, including all participants analyzed as randomized. The primary outcome will be analyzed using multiple regressions with adjustment for MWD, PFWD, and FWD. A mixed ANOVA will be performed to test the mean differences between the three groups (between-subject factor) and over the three measurement points (in-subject factor). Results will be reported as the difference in MWD, PFWD, and FWD from t1 to t2, t2 to t3, and t1 to t3, as well as the mean differences between GE1 and GE2, and ACG with 95% confidence intervals. To determine the minimal clinically important difference (MCID), a change in scores for the primary outcome will be calculated by subtracting the baseline outcome from the t2 (3 months) and t3 (6 months) outcomes for each participant. The least important difference (MID) for improvement and deterioration will be defined by the upper and lower limits of the 95% confidence interval of the mean change in MWD, PFWD, and FWD [71]. Twenty meters was defined as MCID [17]. However, a recent meta-analysis [19] showed significant heterogeneity in the magnitude of effect estimates for MWD (*χ*^2^ = 16.4, *p* = 0.022) and PFWD (*χ*^2^ = 19.6, *p* = 0.003). The mean change (SD) in MWD for patients randomly allocated to home exercise or programs with no exercise plan ranges from 24 (166) to 402 (391) m and PFWD changes range from 21 (81) to 182 (249) m.

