
Finally, secondary outcomes (walking ability and general and specific health-related QoL) will be similarly analyzed. Mediation and moderation analyses will be performed to examine mechanisms of influence (process variables) as well as Structural Equation Modeling (SEM) that will allow the analyses of complex relationships between variables and test causal relationships explaining initial behavioral change throughout time. Measures of effect size and statistical power (1−*β*) will be presented for all statistical tests performed. All planned tests are two-tailed. Statistical significance will be set at *P* ≤ 0.05. IBM® SPSS® V.26 and IBM® IPSS® Amos™ will be used to perform all data analyses.

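### The primary endpoint is stated inconsistently across four places, and the plan names no measure, timepoint or arm contrast that decides the trial

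*Protocol article*

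**What the plan says.** The protocol describes the primary endpoint in four places.

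- **Abstract, Methods:** "The primary outcome will be the change in distances walked (maximal and pain-free) from baseline to 3 and 6 months". Functional walking distance (FWD) is absent and no test is named.
- **Outcomes {12}, Primary outcome:** "change in PFWD, FWD, and MWD measured using a standardized treadmill test and the 6-min walk test (6MWT". This gives three distances on two tests, with no timepoint.
- **Table 1:** MWD, PFWD and FWD are listed against the treadmill. Only PFWD is listed against the 6MWT, although that row says the test "evaluates the functional capacity of the individual to walk over a total of 6 min".
- **Text after Table 1:** the two primary measures are "walking distance measured with the treadmill test and walking distance measured with the 6MWT".

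Statistical methods {20a} gives both multiple regressions and a mixed ANOVA (three groups, three occasions) for the primary outcome. It continues: "Results will be reported as the difference in MWD, PFWD, and FWD from t1 to t2, t2 to t3, and t1 to t3", together with mean differences between the arms and 95% confidence intervals. All tests are two-tailed, and "Statistical significance will be set at" P ≤ 0.05.

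Sample size {14} rests on a single repeated-measures interaction test at 5%. Objectives {7} hypothesises that ExpG2 does better than both ExpG1 and the active control group (ACG). The Abstract's Discussion would take superiority of ExpG2 as evidence that the virtual assistant works, without naming the comparator.

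**The concern.** These are competing current definitions of the primary endpoint. They disagree on how many distances count, which test supplies them and when they are read. An analysis plan could settle this only by overriding one part of the protocol with another.

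Two things are at stake. First, if the distances, tests or arms disagree, the protocol gives no basis for saying what the trial found. Second, the sample size allows for one test at 5%, while the statistical section puts many co-equal results under the same threshold. Some readings of the plan therefore carry a false-positive risk well above 5%.

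The contrast also matters for interpretation. ExpG2 differs from ACG in having the app and in losing face-to-face and telephone contact. Only ExpG2 vs ExpG1 holds the app constant.

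**Working it through.** **1. The definitions side by side**

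| Place | Distances | Test | Timepoint |
|---|---|---|---|
| Abstract | MWD, PFWD | not named | 3 and 6 months |
| Outcomes {12} | PFWD, FWD, MWD | treadmill and 6MWT | none |
| Table 1 | MWD, PFWD, FWD; PFWD | treadmill; 6MWT | – |
| Text after Table 1 | walking distance | treadmill and 6MWT | 3 and 6 months |

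**2. Does the 6MWT fit the definitions?** PFWD ends at pain onset, FWD where the patient chooses to stop, and MWD where pain forces a stop. In the 6MWT the duration is fixed and the patient may rest and resume. Total 6MWT distance is therefore none of the three. Distance at first stop could be recorded, but it is censored for anyone who never stops.

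**3. The plan's own figure.** Sample size {14} gives 57 per group for f = 0.25, 80% power and 5%. With 3 groups, 3 occasions, λ = f²·N·m·ε/(1−ρ), and assumed ρ = 0.5 and ε = 1, N = 36 in total already gives λ = 0.0625 × 36 × 3/0.5 = 13.5 and 82% power. So 57 per group is not reproduced under that setting. The correlation and ε are not stated, so this is a separate matter. What counts here is that the calculation allows for one test at 5%.

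**4. Number of pairwise results** = measures × intervals × arm pairs. The wording on arms permits 2 or 3 pairs.

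- Abstract: 2 × 2 × (2 or 3) = 8 to 12
- Table 1: 4 × 3 × (2 or 3) = 24 to 36
- Outcomes {12}: 6 × 3 × (2 or 3) = 36 to 54

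**5. Chance of at least one false positive when all three arms are equal.** The documents give no correlations. I assume 0.5 between occasions and 0.5 to 0.9 between measures. Arm means were simulated as multivariate normal. Each pairwise difference in change was standardised and called significant if |z| > 1.96. The interaction was tested on 4 degrees of freedom per measure.

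| Reading (Table 1's four measures unless stated) | Chance |
|---|---|
| ExpG2 must beat both arms, same measure and interval | 3–5% |
| Mixed-ANOVA interaction on each measure | 10–16% |
| Any result favouring ExpG2, changes from baseline only | 14–23% |
| Any result favouring ExpG2, three intervals | 20–32% |
| Abstract version, 12 comparisons, either direction | 29–36% |
| All 36 comparisons, either direction, unprotected | 44–64% |

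Higher correlation between measures gives the lower end of each range. Independence would give 1 − 0.95³⁶ = 84% for 36 comparisons and 1 − 0.95⁴ = 18.5% for four interaction tests. These overstate the risk because the results are correlated.

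One measure alone, over three intervals and three pairs (9 comparisons), still gives about 28%. Naming a measure is therefore not enough; the timepoint and contrast must be fixed too.

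**6. Power under each remedy.** Assume a standardised pairwise difference of 0.5.

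| Level per test | 57 per arm | 100 per arm |
|---|---|---|
| 0.05 | 76% | 94% |
| 0.025 | 67% | 90% |
| 0.05/36 = 0.0014 | 30% | 63% |

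**The case against.** The strongest reply is that a reader might infer that every measure, interval and arm pair is formally tested at 5% and that any one significant result counts as success. The text does not go that far. It says the interval and arm differences are reported with confidence intervals. The only between-group test it describes in any detail is the mixed ANOVA, on which the trial is also sized. No success rule is written. The Objectives join the two ExpG2 comparisons, and the Abstract's Discussion refers to the primary and secondary outcomes together. A conjunctive reading is natural and would not inflate the error when all arms are equal. Nor is a false claim for ExpG2 shown to be likely: the 44–64% includes results against ExpG2 and results that do not involve it. Counts in the dozens come from Table 1 and Outcomes {12}, not from the Abstract. All of this stands.

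It is also fair that multiplicity methods and contrast order are often left to an analysis plan, which is not shown. Their absence alone would not be a finding.

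A further tempting claim is that the 6MWT cannot yield FWD at all. That is too strong, since a first voluntary stop can be recorded.

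The reply does not remove the contradiction between the four places. The ANOVA is not described as a gate for the other comparisons, it is named alongside regressions without precedence, and applied to each of four measures it still exceeds 5%. No conjunctive rule is stated.

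**Conclusion.** The point holds as an inconsistency that leaves the primary conclusion undetermined. The four statements of the endpoint cannot all be followed, and the protocol does not say which measure, timepoint, contrast or analysis decides.

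The consequence for false positives is a range, not a single figure: 10–16%, 20–32% or 44–64% depending on the reading, with the last an unprotected worst case. Of the readings calculated, only the one requiring ExpG2 to beat both arms on the same measure and interval stays within 5%. These figures rest on the assumed correlations, on Table 1's four measures and on all three arms being equal. The documents do not support saying that the trial will declare success on any single comparison; they support saying that nothing in the text rules it out.

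**What to change.** Before any comparative results are seen:

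1. Name one primary measure and timepoint, for example the t1-to-t3 change in treadmill MWD, on which the trial already selects and stratifies. The sponsor may prefer another. The Background regards the 6MWT as closer to daily walking, and the treadmill test has a 500 m pain-free limit. If the 6MWT is chosen, call it total 6MWT distance.
2. Name one deciding analysis, either the regression or the mixed ANOVA.
3. Fix the contrasts. Either test ExpG2 vs ExpG1 first at 5% and then, only if it succeeds, ExpG2 vs ACG; or require both, as the Objectives hypothesise. ExpG2 vs ExpG1 should not wait behind ExpG2 vs ACG, because it is the only contrast that holds the app constant and so supports the claim about the virtual assistant.
4. Make the other distances, total 6MWT distance and the 3-month results secondary.
5. Align the Abstract, Outcomes {12}, Table 1 and the text after it.

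The milestone should be the first sight of comparative results, because section {17b} says unblinding will not occur.

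The cost is an amendment to the protocol and registry wording, with no new data. The other distances become supportive. In an ordered scheme, a failed first contrast means the second is not formally tested; requiring both lowers power. In return, each contrast keeps the full 5% level rather than the 0.0014 that splitting alpha over 36 comparisons would need.
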